**Methods:**

This pilot study will follow a prospective randomised controlled design at the Royal Adelaide Hospital and The Queen Elizabeth Hospital (South Australia). This study aims to recruit 60 patients between 18 and 60 years old who will be randomly assigned to either the suprapatellar or infrapatellar approach following a decision for intramedullary surgical fixation by the treating surgeon. All nails in this study will be Stryker T2 Alpha nails. Patients will undergo standard radiograph, magnetic resonance imaging, and clinical assessments in-line with their standard operative care, and complete a number of patient-reported and performance-based outcome measures. Performance-based outcome measures will be assessed utilising three-dimensional motion capture techniques. Follow-up time points are 3, 6, 12, and 18 months. Feasibility outcomes include ability to meet enrolment and retention metrics, compliance with all questionnaires and assessment procedures, and the occurrence of any adverse events. The primary clinical outcome is the incidence of anterior knee pain at 12 months after surgery.

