### Tertiary objectives

The tertiary objective of the study is to explore the development of novel three-dimensional (3-D) motion capture based biomechanical outcome measures for assessing AKP and knee function after tibial fracture surgery. This will be achieved by evaluating objectively measured biomechanical outcomes and gait patterns against patient-reported outcome measures of knee pain and function.

Additional objectives include comparing the effect of SPN versus IPN on surgical outcomes including: tibial alignment, rotational profile, intra-articular damage, and time to union.

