### Participant flow timeline

The timeline for participant involvement in the trial is detailed in Fig. 1. Following randomisation, baseline patient assessment will be completed using an online form (note: this data is not affected by the randomisation allocation). Surgery will proceed at the earliest available opportunity in line with each hospital’s routine clinical practice. Operative information will be recorded using an online form. Recruitment, medical, and surgical data collection will occur at the Royal Adelaide Hospital and The Queen Elizabeth Hospital. Follow-up appointments will be scheduled such that medical imaging, clinical reviews, and gait laboratory assessments coincide. The first clinical review will occur at the treating institution, with all subsequent appointments at the Clinical Research Facility at The University of Adelaide. At each follow-up, patients will present for medical imaging at a diagnostic imaging practice (lateral and anteroposterior radiographs at all follow-ups; magnetic resonance imaging (MRI) at 6 and 12 months); followed by clinical examination with an orthopaedic and trauma specialist; finally, PROMS will be collected using an online form and gait laboratory assessments conducted at the Clinical Research Facility, Adelaide Health and Medical Sciences Building (all follow-ups except 6 weeks). At the conclusion of the gait laboratory assessments, participants will be provided a wrist-worn activity monitor to be returned after 7 days with a reply-paid envelope.

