#### Postoperative outcome measures

Additional objectives of the study include comparing the effect of surgical outcomes; postoperative outcome measures include:Tibial alignment from post-operative lateral and anteroposterior radiographs (all follow-up time-points),Time to union as indicated on post-operative radiographs,Rotational profile from MRI (6 and 12 months follow-up),Intra-articular damage from MRI (6 and 12 months follow-up),Subsequent surgeries and complication rate (e.g. compartment syndrome, surgical site infection, malunion, nonunion, screw penetration in the tibiofibular joints),Fracture location will also be recorded as this may influence outcomes.

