##### Return to work

As time from surgery as indicated at any of the follow-up time-points. We will also record any changes to occupation or working capacity resulting from the leg injury or from AKP.

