As this is a pilot study, any analyses related to the clinical outcomes should be treated with caution and viewed as exploratory. All clinical outcome measures will be assessed descriptively (means and standard deviations for normally distributed continuous variables; medians and interquartile ranges for non-normal continuous variables; frequencies and percentages for categorical variables). Missing data will be tabulated.

Logistic regression models will be used to determine the association between surgical approach and AKP 12 months post-surgery. Models will be adjusted for age and gender with hospital included as a fixed effect. The results will be reported as odds ratios with 95% confidence intervals.

Secondary clinical outcomes will be analysed using linear regression models for continuous outcomes or generalised linear models for count or categorical outcomes. Generalised estimating equations will be used to account for correlation due to repeated measures over time, and a time-by-surgery interaction term will be included to test for differences in the relationship between surgical approach and outcomes over time. If assumptions about distributions are not met (e.g. non-normally distributed continuous outcomes) alternative approaches will be explored as appropriate, including transformations or non-parametric modelling.

To assess differences between cases and matched healthy controls, logistic regression models will be used to determine the association between treatment (surgery versus no surgery) and AKP 12 months post-surgery. Models will be adjusted for the matching variables age, gender, and body mass index, with hospital also included as a fixed effect.

To determine novel predictors of functional outcomes, logistic regression prediction models will be used to assess the discriminatory power of PROMs and PBOMs at assessing AKP and other functional measures. Estimates of discrimination (area under the curve, sensitivity, and specificity) will be used to rank combinations of outcomes in ability to predict AKP. Principal component analysis (PCA) will be explored as a method of data reduction to allow information from a larger number of variables to be included in the predictive model. If PCA is successful, a predictive model will be fitted using an appropriate number of principal components (determined using the proportion of variance explained as well as number of events in the dataset) as predictors.

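### Time to union is interval- and right-censored, but the stated model for continuous secondary outcomes is linear regression, so by default the contrast covers only patients who united

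*Protocol article*

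**What the plan says.** The Tertiary objectives section of the protocol article adds a comparison of SPN with IPN on "tibial alignment, rotational profile, intra-articular damage, and time to union". The Postoperative outcome measures section, under the secondary clinical outcomes, lists "Time to union as indicated on post-operative radiographs". Its list of complications includes "surgical site infection, malunion, nonunion".

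The Participant flow timeline places "lateral and anteroposterior radiographs at all follow-ups". The Abstract states "Follow-up time points are 3, 6, 12, and 18 months". The timeline's remark that gait laboratory assessments take place at "all follow-ups except 6 weeks" implies a further early visit.

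For the analysis, the Statistical analysis section states: "Secondary clinical outcomes will be analysed using linear regression models for continuous outcomes or generalised linear models for count or categorical outcomes". It adds generalised estimating equations for repeated measures. If distributional assumptions fail, it allows alternatives such as transformation or non-parametric modelling. Missing data are to be tabulated, and every outcome is to have an effect estimate with a 95% confidence interval. The section labels all clinical analyses exploratory.

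**The concern.** A time to an event that is seen only at visits is known only to lie between two radiographs, here up to 6 months apart. For a patient with nonunion, or one lost before union, it is known only to exceed the last radiograph. A linear model needs one number per patient. Patients without a union time have none, so standard software omits them, and the others enter with the date of the visit at which union was first seen.

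The contrast is then conditional on having united, which is a post-randomisation event that the approach may itself affect. The arms compared are no longer the randomised arms, and any difference in nonunion is lost from this estimate. The Discussion expects the clinical outcomes to supply preliminary effect sizes and power calculations for the full trial. A union-time effect estimated this way would carry its bias into that design.

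**Working it through.** **Which model applies.** The article gives no union-time figure to reproduce, so the first step is to read the sections together.

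- Time to union is a duration, one value per patient. Among the stated options the natural one is linear regression.
- Generalised estimating equations handle repeated measurements. A single duration per patient is not repeated.
- The fallback is triggered by distributional shape. A transformation cannot supply a time that was never observed.
- No censoring rule is given, and tabulating missing data does not put patients back into the estimate.

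**Inputs for an illustration.** From the article: 25 completers per arm; radiographs at 6 weeks (1.5 months, implied) and at 3, 6, 12 and 18 months. Assumed: lognormal union times with log-SD 0.45 and median 5 months among those who unite; nonunion rates as shown.

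**Visit-dated mean among united patients.** With median 5, the probabilities of first being seen united at the five visits are 0.0037, 0.1244, 0.5292, 0.3168 and 0.0236 (sum 0.9978).

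- Mean visit date = (0.0037×1.5 + 0.1244×3 + 0.5292×6 + 0.3168×12 + 0.0236×18) / 0.9978 = 7.80 months.
- True mean = 5 × exp(0.45²/2) = 5.53 months. Visit dating therefore adds about 2.3 months to each arm's mean.

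**Nonunion 5% v 20%, equal times among those who unite.**

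- Expected patients with nonunion: 25×0.05 + 25×0.20 = 6.25 of 50. Simulation (4,000 trials) gives 6.3 without a union time, because a few unite after 18 months.
- Linear contrast: 7.80 − 7.80 = 0 months (simulation 0.03). This follows directly from assuming equal times. It shows that the estimate is blind to nonunion and says nothing about how large the effect would be in this trial.
- For comparison, set patients not united at 18 months to 18. The arm with 5% nonunion has a fraction united of 0.95×0.9978 = 0.948 and a mean of 0.948×7.80 + 0.052×18 = 8.33. The arm with 20% has 0.80×0.9978 = 0.798 and 0.798×7.80 + 0.202×18 = 9.86. The difference is 1.5 months (simulation 1.54).
- At 5% v 10% the same comparison gives about 0 v 0.5 months.

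**Direction can reverse.** Give the 20% arm a median of 4.5 months. Its visit-dated mean is 7.08, so the linear contrast is 7.08 − 7.80 = −0.7 months, in favour of the arm with more nonunion. With patients not united kept at 18 months (fraction united 0.80×0.999 = 0.799), its mean is 0.799×7.08 + 0.201×18 = 9.27, and 9.27 − 8.33 = +0.9 (simulation +0.97).

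**Visit dating alone.** With gamma union times and no nonunion, visit-dated v true mean difference in months:

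- Medians 5 v 4: 1.23 v 1.19 at shape 2 (+3%); 1.50 v 1.06 at shape 6 (+42%).
- Medians 7 v 6: 0.79 v 1.19 at shape 2 (−34%); 1.20 v 1.06 at shape 6 (+14%).

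The distortion has no fixed size or sign, so no single percentage should be quoted.

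**The case against.** The best reply is that the article never classes time to union as continuous and never says that patients without union are excluded. Its sentence on models is generic and covers many outcomes. United or not at each radiograph is a repeated categorical outcome, and a complementary log-log model by visit interval is itself a binomial generalised linear model, so the remedy lies within a family the plan already names. This stands in part: exclusion is the default consequence, not a stated rule, and the plan's options are wider than linear regression. But the outcome is defined as a time and not as status by visit, and nothing directs the analyst to the discrete-time form.

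A reader might infer that nonunion disappears from the comparison of the arms. It does not. Nonunion is a listed complication, and every outcome is to have an effect estimate with an interval, so an excess would be reported there. The loss is confined to the time-to-union estimate.

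A reader might also extend the point to return to work, recorded "As time from surgery as indicated at any of the follow-up time-points". The article lists it under Covariates and assigns no between-arm model to it, so the criticism does not reach it.

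Finally, outcome-specific detail is often left to an analysis plan. That would answer a silent article, but this one assigns model families to all secondary clinical outcomes.

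**Conclusion.** The point holds in a limited form. Followed as written, the stated model most naturally gives a visit-dated comparison among united patients, into which a difference in nonunion does not enter. Under assumed nonunion of 20% v 5% with equal times among those who unite, that contrast is about 0 months. If the arm with more nonunion also has somewhat faster unions, it can look better on this measure. These figures rest on assumed union times and nonunion rates, because the article supplies neither. They show the mechanism and do not predict this trial's results.

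Severity is minor. Time to union is an additional objective, the clinical analyses are exploratory, and none of the Table 2 progression criteria uses it. The exploratory label warns of imprecision, however. It does not remove a bias whose mechanism is known in advance.

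**What to change.** Add two or three sentences to the Statistical analysis section:

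- Analyse time to union with a discrete-time model (binomial generalised linear model, complementary log-log link, one record per patient and visit interval) or an interval-censored model, adjusted for age, gender and hospital as in the primary clinical model.
- Keep patients with nonunion in the analysis as not united. Censor patients lost to follow-up at their last radiograph.
- Report the proportion united by visit and arm, with 95% confidence intervals.

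In the illustration above, the last item would show the difference that the linear model misses. At 12 months the cumulative probability among those who unite is 0.0037 + 0.1244 + 0.5292 + 0.3168 = 0.974, so the proportions united are 0.95×0.974 = 92.5% and 0.80×0.974 = 77.9%, a gap of about 15 percentage points. With 25 per arm its standard error is √(0.925×0.075/25 + 0.779×0.221/25) = 0.098, about 10 points, so it remains descriptive.

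The cost is slightly more analysis work with standard software and no new data. Intervals with very few unions may have to be merged: under the assumptions above, 50 × 0.0037 = 0.2 unions at most are expected by 6 weeks.

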One well-documented disadvantage of IM nailing is long-term anterior knee pain (AKP), occurring in 10% [10] to 86% of cases [11]. AKP post-SPN has been reported as non-existent [5], significantly lower than IPN [8], and not different to IPN [12–15]. These differences may in part be explained by differing study designs and the range of scoring systems used being developed for various other knee pathologies [16–19]. AKP can severely influence long-term activities of daily living [20–22], of which, kneeling causes the most severe knee pain [23], and exacerbates existing pain in 60% of cases [24]. This has potentially significant effects for occupations that require kneeling, as well as some religious activities. The incidence of knee pain resulting from kneeling varies [11, 23, 25, 26] but is reported to be as high as 91.8% [27]. Further, 26 [28] to 50% [27] of patients are unable to kneel at all. Two different forms of kneeling have been described: upright and flexed [29, 30]. This results in different anatomical structures contacting the ground [30] which is likely to influence the incidence of AKP. In order to assess kneeling ability, it is important to consider both forms [31]. To date, there have been four randomised, prospective trials looking at SPN versus IPN [8, 14, 32, 33]; only one study [33] assessed kneeling ability but failed to differentiate between kneeling modalities. No research has explored how biomechanical changes in kneeling might relate to AKP after IM nailing.

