##### KOOS patellofemoral subscale [47] (KOOS-PF)

The KOOS-PF contains 11 items that generate a normalised score from 0 to 100, similar to the KOOS. The subscale was developed for AKP/patellofemoral pain and/or patellofemoral osteoarthritis. The KOOS-PF is suitable to be used in conjunction with the KOOS [47]. The MCID for the KOOS-PF is 11.8 [47].

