### Exploratory clinical outcomes

The tertiary objective of this study is the development of novel outcome measures specific to IM nailing of tibial shaft fractures from a series of performance-based and patient-reported outcomes captured in the pilot RCT. The successful development of the new tool using a combination of PROMs and PBOMs will be assessed on its ability to differentiate participants with and without AKP.

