### Sample size

This study has been designed as a pilot study to determine the feasibility of a large-scale RCT. Therefore, no sample size calculation was performed. Based on the number of fractures in a year at the recruitment sites, we aim to recruit a total of 60 patients; allowing for some loss to follow-up, should enable 25 patients to complete follow-up assessments from each group (SPN and IPN), which is in-line with sample size recommendations for pilot studies [72].

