The aetiology of AKP remains unclear [86], yet the choice of approach may play an important role: patients undergoing SPN may be more prone to loss of quadriceps function and damage to intra-articular structures; whereas IPN patients may suffer from increased likelihood of damage to the patellar tendon, fat pad, and saphenous nerve. A meta-analysis of 20 papers found an average of 47% of patients reported AKP at an average follow-up of 2 years, although how the AKP was assessed was not detailed in the review [87]. Common modalities used to assess knee pain after tibial shaft nailing include the Lysholm Test [17], Oxford Knee Score [18], and the Kujala Score [19]; none of these tools are specific to AKP after tibial nailing. Further, simply asking whether any pain exists is frequently used [25, 88–91], but the use of such a binary measure is problematic for future studies as large numbers of participants are required in order to power the study, e.g. if there is truly no difference between IPN and SPN treatment (assuming absence of AKP is 53% in both groups), then 1080 patients are required to be 90% sure that the limits of a two-sided 90% confidence interval will exclude a difference between groups of more than 10%.

An important factor when considering PROMs, such as kneeling ability, is the potential disparity between patients’ perception and their actual ability to perform the activity. Though comparable studies for IM nailing are lacking, the inability of PROMs to detail patient recovery sufficiently after total knee arthroplasty has been well described [92–95]. Hassaballa et al. found 37% of patients believed they had the ability to kneel following IM nailing, but 81% could kneel upon instruction [96]. The current study, to the authors’ knowledge, is the first study aiming to collect both patient-reported and 3-D motion capture based outcomes for this cohort.

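### The exploratory AKP tool is chosen and judged on discrimination in the same roughly 50 pilot patients; without correction for selection and fitting, that discrimination will be overstated and the ranking unstable

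*Protocol article*

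**What the plan says.** Two sections of the protocol article set the rules.

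- **Selection** (Statistical analysis): logistic prediction models are fitted to patient-reported outcome measures (PROMs) and performance-based outcome measures (PBOMs), and "Estimates of discrimination (area under the curve, sensitivity, and specificity) will be used to rank combinations of outcomes in ability to predict AKP". Data reduction by principal component analysis (PCA) is to be explored. If it works, the number of components depends on variance explained and on the number of events.
- **Success** (Exploratory clinical outcomes): the tool is to be built "from a series of performance-based and patient-reported outcomes captured in the pilot RCT", and its successful development "will be assessed on its ability to differentiate participants with and without AKP". No threshold is given.

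The Sample size section says "we aim to recruit a total of 60 patients" and expects 25 completers per group. No other sample is named for developing or testing the tool.

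The article also says that clinical analyses are exploratory and to be read with caution, and that 95% confidence intervals will accompany all effect estimates.

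**The concern.** The same quantity, measured in the same patients, both picks the combination and decides whether the tool works. A model's AUC in the data used to choose and fit it is biased upwards. The bias grows with the number of combinations compared and shrinks with the number of events. Here the candidates are many and the events few.

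There is a second, related difficulty. AKP is defined by three yes/no answers from the patient (Primary clinical outcome measure). Of KOOS-PF the article says: "The subscale was developed for AKP/patellofemoral pain and/or patellofemoral osteoarthritis". The VAS is self-rated usual pain over the last week. These instruments overlap with the outcome, so they are likely to rank high whatever motion capture contributes. A single ranking that pools PROMs and PBOMs need not show whether the biomechanical measures add anything, which the Discussion itself lists as unknown.

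The Background expects biomechanically validated measures to be used in a full-scale trial, and the Discussion calls a binary AKP endpoint problematic because of the numbers it needs. An overstated AUC could therefore carry a weak tool into the definitive trial.

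**Working it through.** **The plan's own figures.** The article states no figure for the prediction tool. Two related figures reproduce.
- Completers: 2 × 25 = 50 of 60, or 83.3%, an implied loss of 10/60 = 16.7%.
- The Discussion's 1080 patients for binary AKP: n per arm = (1.645 + 1.645)² × 2 × 0.53 × 0.47 / 0.10² ≈ 539.2, rounded up to 540; 2 × 540 = 1080.

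**Inputs.**
- N = 50 (Sample size).
- AKP prevalence 47%, from the Discussion's meta-analysis: 0.47 × 50 = 23.5, taken as 24 with AKP and 26 without.
- Range 10% to 86% (Background and rationale): 0.10 × 50 = 5 and 0.86 × 50 = 43 cases.
- Number of candidates: not stated, so assumed to be 20, with 10 and 12 as lower variants. For scale, the questionnaire and clinician scores listed are KOOS 5, KOOS-PF 1, FJS-12 1, EQ-5D-5L 2, VAS 1, PCS 1 and KSS 2, which makes 13. About a dozen functional tests follow, before any gait, EMG or modelled-force parameter is counted.
- Search: also assumed. All singles, all pairs (20 × 19 / 2 = 190) or, for 12 candidates, all triples (12 × 11 × 10 / 6 = 220).

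**Method.** Candidates are simulated as pure noise, independent or with a common correlation. The combination with the highest in-sample AUC is chosen and fitted by logistic regression, and its apparent AUC is compared with its AUC in 1000 new patients. Optimism is apparent AUC minus AUC in new patients.

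**Results with selection (24 cases of 50).** AUC in new patients is about 0.50 in every row.

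| Search | Mean apparent AUC | Share with AUC ≥ 0.70 |
|---|---|---|
| Best single of 20 | 0.66–0.68 | 20–23% |
| Best pair of 20 | 0.73 | 78–86% |
| Best pair of 10 (correlation 0.5) | 0.70 | 48% |
| Best triple of 12 (correlation 0.3) | 0.74 | 79% |

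At correlation 0.5, the best single of 20 averages 0.77 with 5 cases and 0.72 with 43.

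**Results without selection.** A fixed model with 2, 5 or 10 noise predictors or components gives 0.60, 0.67 or 0.75. With all 60 patients (28 cases) the figures are 0.59, 0.66 and 0.73.

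**Does an ordinary confidence interval protect?** With the Hanley–McNeil standard error and 24 against 26 patients, the naive 95% interval excludes 0.5 once the apparent AUC reaches 0.654. Under pure noise this happens in 52–71% of datasets for the best single of 20, 84% for the best pair of 10 and over 99% for the best pair of 20 (both pair figures at correlation 0.5).

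**Does resampling help?** For the best pair of 20 at correlation 0.5, a bootstrap that repeats the selection lowers the mean from 0.73 to 0.57 (40 datasets, 15 resamples each). It removes (0.73 − 0.57) / (0.73 − 0.50) = 0.16 / 0.23, about 70% of the optimism.

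**The case against.** The strongest reply is that the defect is inferred from silence. The article never says the estimates are uncorrected, and internal validation is a detail that a full protocol or statistical analysis plan could hold. That stands as a limit: if the unseen document already corrects for optimism, only the wording here needs to follow. It does not dispose of the point, because the article does more than leave a gap. It states a ranking rule and a success rule, and both, followed as written in the one sample named, give biased results.

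A reader might go further and infer that the success test can hardly fail, or that the tool would look successful even if no measure carried signal. The documents do not support this. No threshold is set, so passing cannot be defined. For the best single of 20 noise measures, the naive interval still includes 0.5 in 29–48% of datasets. Zero signal is also unrealistic, because pain questionnaires that overlap with AKP will carry signal. The candidate count and the all-subsets search are assumptions, not protocol text.

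The PCA route would restrain the problem (0.60 for two fixed components), but it is only to be explored and does not replace the ranking. The exploratory label invites caution without correcting an estimate, and ordinary confidence intervals ignore the selection. Combining PROMs and PBOMs is the stated intention and not an error; reporting PBOMs separately is an addition to it.

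**Conclusion.** The concern holds in a limited form. The stated ranking and success rules use the same discrimination in the same roughly 50 patients. Unless it is corrected for selection and fitting, discrimination will be overstated and the order of the combinations unstable.

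The noise results bound the problem and do not forecast it. Optimism is about 0.10 in AUC for a fixed two-component model (0.60 − 0.50), about 0.16 to 0.18 for the best single of 20 and about 0.23 for the best pair of 20. These rest on 50 patients, 24 cases, an assumed candidate list and an assumed exhaustive search.

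Only the tertiary, exploratory objective is affected. No progression criterion in Table 2 uses the tool, so this is a recommended improvement and not a must-fix.

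**What to change.** In Statistical analysis and Exploratory clinical outcomes:

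1. Rank the combinations and judge the tool on optimism-corrected discrimination, by bootstrap or repeated cross-validation, with variable choice, PCA and cut-point repeated inside each resample.
2. Report the corrected AUC with a confidence interval that reflects the selection.
3. State that some optimism may remain (0.57 against a true 0.50 in the check above) and that the tool needs external validation before use in the full trial.
4. Report discrimination for PBOMs alone, and their gain over the pain questionnaires, because KOOS-PF and VAS overlap with the self-reported AKP outcome.

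Penalised regression is a reasonable option but not a requirement. The cost is a paragraph of wording and some analysis code, with no new patients or data. The downside is that the reported discrimination will be lower.
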